## Ethics and dissemination

### Research ethics approval

The trial has been approved by the University of Copenhagen Research Ethics committee for Science and Health (ref. 504–0111/195000). This trial does not involve collecting biological specimens for storage.

### Protocol amendments

The trial will be conducted in accordance with the protocol. If modification is required, the funder will be notified, followed by the clinics involved in the project. Significant changes will be registered here: https://clinicaltrials.gov/ct2/show/NCT04129359. Minor changes, seen as administrative rectifications to the protocol with no effect on the conduct of the trial will be agreed upon by the project management group.

### Access to data

After our primary publication of the trial results, a version of the data will be shared on a public platform and made available for research in accordance with Danish law about the protection of personal data.

## Discussion

This cluster-randomised controlled study aims to test the effectiveness and feasibility of an intervention to increase mental well-being and resilience in new mothers and their offspring. GPs and staff received brief training in the core concepts of the web-based resilience training programme. From October 2019 to March 2020 70 GPs/staff were trained and subsequently included pregnant women in the study. An obvious shortcoming of the study might be related to COVID-19, since a large proportion of antenatal and postnatal contacts were reported to be affected by the pandemic. GPs and staff reported that pregnant women’s major concerns were infection and infection-related risks. This delimited the clinicians’ window of opportunity to put mental well-being and mentalisation on the agenda during consultations, and the robustbarn.dk intervention might have been introduced with less enthusiasm than might have occurred otherwise due to other competing tasks in the clinic.

### Strengths

The location of this pragmatic cluster-randomised trial in Danish general practice, with its typically high levels of engagement with preventive obstetric and child developmental assessments, is likely to create a robust sample with relatively low levels of attrition assuming patients remain registered with their original GP. Recruitment of consecutive patients attending their first antenatal appointment should provide a sample representing a typical clinical caseload for participating practices. The flexibility given to clinicians in terms of signposting their patients towards the web-based resources should reflect potential future real-world practice underpinned by progressive universalist principles [66] and the quantitative process evaluation of website usage will allow assessment of equity of access to the resources. The strength of Danish population registers will ensure reliable long-term follow-up data for almost all participants.

### Limitations

It was necessary to exclude non-Danish-speaking women from participation for pragmatic reasons, and this will reduce the generalizability of findings to migrant populations.

It is possible that there may be variation in recruitment rates across practices — with some practices generating selective samples, while others may recruit almost all eligible women [67]. Similarly, there may be variation across practices in the extent to which the intervention is presented to participants. Given the design of the trial, these factors may increase clustering effects and potentially reduce statistical power.

There may be some dilution of the intensity of intervention if participants change practice or consult with untrained clinicians within their existing practice.

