#### Randomisation of GPs

After completion of GP recruitment but before the training course, GP clinics were randomised to the intervention or the control group. Randomisation was performed by an external statistician using a computer-generated randomisation sequence (evt indsætte navnet på programmet).

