##### Identification and recruitment of pregnant women

GPs participating in the trial consecutively invited all pregnant women attending their first antenatal assessment, usually in gestation weeks 6–10. Each practice was asked to recruit a minimum of 10 and a maximum of 30 consecutive participants at their first pregnancy assessment starting October 2019. Data were recorded for women who declined participation, and participation rates were monitored carefully.

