#### Ensuring adherence

To improve adherence to the protocol, quarterly emails are sent to all participating GPs by the research team enquiring about any problems encountered concerning trial-related tasks. The emails include information on numbers of recruited participants and solutions to potential problems connected to data registration. GPs were paid 1000 Danish Kroner per recruited patient for the clinical time used in the 3-year study period. To secure adequate participant enrolment we asses inclusion every month. All participating GPs receive reminders about the project with regular intervals and those with low inclusion numbers were asked if they needed help with practical issues. To ensure representative enrolment all GPs are asked to make notes about pregnant women who were eligible, but not included. The pregnancy consultation used for inclusion has a special billing code and at the end of the study, it will therefore be possible to perform a register-based analysis of non-participation.

To ensure adherence among the participating pregnant women, three-monthly newsletter emails were distributed during the first 1 year of the project. The newsletter provides updates from the research team and access to an official project website (familietrivsel.dk).

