#### Allocation, sequence generation, and concealment

The study is a cluster randomised controlled trial with the general practice as the unit of randomisation. General practices were randomised on a 1:1 basis to intervention or control groups using a computer algorithm. The computer randomised allocation sequence was concealed until all general practices were assigned.

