#### Blinding (masking)

The design is open label with only the study statistician being blinded under the dataset locked after collection of primary outcome data so un-blinding will not occur.

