#### Statistical methods

Binary valued outcomes will be analysed in logistic regression and continuously valued outcomes will be analysed in linear regression. To account for clustering within practices and for possible repeated measurements, generalised estimating equations (GEE) will be employed to adjust the covariance matrix. Possible differential dropout will be adjusted for using inverse probability weighting [61].

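### Women were recruited after allocation by GPs who knew their arm, so selective recruitment can bias the SDQ and CDI comparison; the protocol names only clustering and power

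*Protocol article*

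**What the plan says.** All references are to the Protocol article.

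- **Order of events.** Under Randomisation of GPs: "After completion of GP recruitment but before the training course, GP clinics were randomised to the intervention or the control group". The Discussion gives the next step: "From October 2019 to March 2020 70 GPs/staff were trained and subsequently included pregnant women in the study".
- **Masking and concealment.** Under Blinding (masking): "The design is open label with only the study statistician being blinded". The concealment statement covers practices only: "The computer randomised allocation sequence was concealed until all general practices were assigned".
- **Recruitment of women.** Under Identification and recruitment of pregnant women: "GPs participating in the trial consecutively invited all pregnant women attending their first antenatal assessment". The same section says that data were recorded on women who declined and that participation rates were monitored.
- **What differs at that visit.** Under Robustbarn.dk, GPs introduce the website to all intervention women at the first antenatal appointment, and included women then receive a login. Control women have no access.
- **Checks on non-participation.** Under Ensuring adherence, all GPs are asked to note eligible women who were not included. Because the inclusion visit has its own billing code, "it will therefore be possible to perform a register-based analysis of non-participation". The stated purpose is representative enrolment.
- **Analysis.** Statistical methods gives regression with GEE for clustering, and then: "Possible differential dropout will be adjusted for using inverse probability weighting".
- **Consequence drawn.** Limitations says that some practices may recruit selected groups of women while others recruit nearly everyone, and that the intervention may be presented to differing extents. It concludes that "these factors may increase clustering effects and potentially reduce statistical power".

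**The concern.** Randomising practices makes the practices comparable, and with them the women who would attend them. It does not make the recruited women comparable if recruitment depends on an allocation that is already known. Here GPs who knew their arm judged eligibility and made the invitation. Two exclusions call for judgement: Danish too limited for the questionnaires or the intervention, and a plan to move practice. The first has fuller practical content in the arm that has a website to use. What a woman is offered at the recruitment visit also differs by arm, so acceptance may differ too.

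If the arms end up with different mixes of families, mean SDQ and CDI scores can differ with no intervention effect. More data do not cure this. A GEE working covariance or robust variance changes the standard error, not this shift. Weights for dropout restore the women who were included and then lost, not those who were never included. By naming only clustering and power, the Limitations leave out the consequence that affects the validity of the estimate.

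**Working it through.** **Step 1. Reproduce the plan's sample size, to obtain a standard error.** Inputs from Sample size: 2 SDQ points = 0.3 SD, 80% power, 2.5% significance level, ICC 0.02, 60 clinics, about eight children per clinic, 488 children analysed.

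- Per arm, two-sided: n = 2(2.241 + 0.842)² / 0.3², rounded up to 212, so 424 in total.
- Design effect: 1 + (8 − 1) × 0.02 = 1.14, giving 424 × 1.14 = 483. With 488/60 = 8.13 per clinic it is 1.143, giving 485.
- The plan states 488, so its figure reproduces within rounding as a two-sided 2.5% test. Power at 488 is 80.5%.

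**Step 2. Standard error of the SDQ difference.**

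- SD = 2 / 0.3 = 6.67 points.
- SE = 6.67 × √(2 × 1.143 / 244) = 0.645 points.

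**Step 3. Choose a risk contrast.** The documents give no between-arm imbalance, so both the contrast and the imbalance are assumptions. Primary outcome gives one usable figure: SDQ scores about 2 points higher in the most than in the least deprived quintile in one city.

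- *Contrast 2 points*: each extra most-deprived family replaces a least-deprived one. This is the extreme case.
- *Contrast 1.25 points*: each extra most-deprived family replaces an average family from the other four quintiles, assuming equal steps. Scores relative to the least deprived are 0, 0.5, 1, 1.5 and 2. The mean of the first four is 0.75, and 2 − 0.75 = 1.25.

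**Step 4. Effect on the test.** Bias b = imbalance × contrast. With no true effect, the rejection rate is 1 − Φ(2.241 − b/SE) + Φ(−2.241 − b/SE). With a true 2-point effect and bias against it, power is Φ((2 − b)/SE − 2.241).

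| Assumed imbalance | Contrast | b (points) | b/SE | Type I error | Power, bias against effect |
|---|---|---|---|---|---|
| none | – | 0 | 0 | 2.5% | 80% |
| 10 percentage points | 1.25 | 0.125 | 0.19 | 2.8% | 75% |
| 25 percentage points | 1.25 | 0.3125 | 0.48 | 4.3% | 65% |
| 10 percentage points | 2 | 0.2 | 0.31 | 3.2% | 71% |
| 20 percentage points | 2 | 0.4 | 0.62 | 5.5% | 59% |
| 25 percentage points | 2 | 0.5 | 0.78 | 7.3% | 53% |

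**Step 5. Compare with the consequence the plan does name.** If clustering raised the ICC from 0.02 to 0.05, the design effect would be 1 + 7.13 × 0.05 = 1.357 and power about 73%. At an ICC of 0.10 it would be 1.713 and about 61%. These ICCs are also assumed. The power loss from bias is of similar order, but bias can also raise the false-positive rate, whereas greater clustering that the analysis allows for only costs precision.

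The documents give no SD or risk contrast for the CDI, so the illustration covers the SDQ only. The mechanism is the same for both outcomes.

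**The case against.** The case for the plan has substance.

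- **Discretion is limited.** Invitation was to be consecutive and to include every woman at her first visit. Both arms had the same minimum of 10 and maximum of 30 (Table 1), and families with other significant difficulties remained eligible. Control GPs attended the same assessment course, so both arms were alerted to psychosocial risk. This stands, and it reduces the risk. It does not remove it, because the Limitations themselves allow that some practices may recruit selectively.
- **The Limitations sentence is not false.** Variation between practices can increase clustering. This stands; the sentence is incomplete.
- **Detail may be elsewhere.** By-arm recruitment tables and covariate lists are often left to a full protocol or analysis plan, neither of which is shown. Their absence from a condensed article is therefore not the point. The point is that the visible text draws an incomplete conclusion from a risk it recognises, and that the corrections it states concern other problems.
- **The illustration leans towards the large side.** The 2-point contrast is between extreme quintiles, and 25 percentage points is a very large imbalance for a group that is a fifth of its reference population. This stands, hence the smaller contrast alongside it.

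A reader might also infer that nothing is planned to detect selective recruitment. The documents do not support that: decliner data, monitored participation, notes on eligible women not included, and a possible register analysis are all described. Nor does the payment of DKK 1000 per recruited woman show a difference between arms. It is stated for GPs without distinction by arm, so it rewards volume in both.

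**Conclusion.** The point holds as a risk that the plan recognises only in part. Allocation was known at recruitment, and the offer at the recruitment visit differed by arm. The Limitations mention clustering and power but not bias, and the stated analysis does not act on who entered the trial. The existing non-participation data could address much of this, but are not said to be compared by arm or used in the primary comparison.

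A reader might go further and conclude that the SDQ and CDI results will be biased. The documents do not support that, because they show no imbalance and consecutive invitation works against one. The direction of any bias is also unknown. Under the assumptions above, type I error moves from 2.5% to between about 2.8% and 7.3%, with the upper end needing both the extreme contrast and a very large imbalance. The SD, ICC and number of children are the plan's own; the imbalances are assumed, as is the even-step spread behind the 1.25-point contrast.

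This does not undermine the design and is not a must-fix. It is worth correcting before outcomes are examined by arm, because a choice of adjustment made afterwards would be less credible.

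**What to change.** 1. **Adjust both primary models.** Prespecify for SDQ and CDI a short set of prognostic maternal characteristics that the first-visit introduction cannot change. Examples are education (baseline demographic questionnaire), adverse childhood experiences (Table 2, enrolment) and age or earlier history from registers. Avoid baseline measures that the introduction might already have influenced, such as prenatal reflective functioning. Adjustment removes only imbalance carried by the measured characteristics.
2. **Make the non-participation analysis definite and by arm.** Use the billing code to list first antenatal visits in each practice during its own recruitment window. Report by arm the fraction recruited and the register characteristics of recruited and non-recruited women. Then add a sensitivity analysis of SDQ and CDI that weights for participation as well as dropout. Language and plans to move may not be visible in registers, so the GPs' notes on women not included should be used alongside.
3. **Amend the Limitations.** State that selective recruitment after allocation can bias the comparison between arms as well as reduce power.

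If an analysis plan already contains items 1 and 2, a cross-reference and item 3 are enough. The cost is a little register programming and analysis work on data that the protocol already describes, with no new participants or visits.

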## Trial status

Protocol version 2, 23.09.2020.

Initiation of recruitment of patients by October 2019. Expected to be completed before the end of 2022.

The SPIRIT checklist and timeline have been included as additional information and in the text.

## Data Availability

The research team will have full access to all data.

## Abbreviation

GP: General practitioners
